### All participants must have a ketone meter

### When to check for ketones

- \*Nausea/vomiting and unable to drink liquids for more than 1 hour
- \*Temperature  $>38^{\circ}\text{C}$
- \*If you are going to the Hospital for any reason
- \*If you are sick for any reason
- \*Blood glucose  $>16.6\text{ mmol/L}$  (300 mg/dL) for more than 2 hours or  $>22.2\text{ mmol/L}$  (400 mg/dL) at any point

### Elevated Ketones

- \*If ketones  $<0.6\text{ mmol/L}$ , treat high blood glucose as you would normally treat
- \*If Ketones  $<0.6\text{--}0.9\text{ mmol/L}$ : make sure that the infusion site is in place. Change infusion site if blood glucose  $>13.9\text{ mmol/L}$  (250 mg/dL) for more than 2 hours. You may give insulin injection by insulin syringe or insulin pen till blood glucose is  $<10\text{ mmol/L}$  (180 mg/dL) (keep the pump off and restart once glucose is  $<10\text{ mmol/L}$  [180 mg/dL]).
- \*Drink water freely as much as you can
- \*Ketones:  $1\text{--}1.5\text{ mmol/L}$ : If you can drink liquids, please follow the guidelines mentioned above. Contact your study staff if you are unable to drink liquids.
- \*Ketones  $>1.5\text{ mmol/L}$ : call your study staff and go to the emergency room if you cannot drink liquids and are dehydrated.

## Annex 6. Clinical Laboratory Test

| Clinical Laboratory Test             |                                                                  |
|--------------------------------------|------------------------------------------------------------------|
| Hematology                    | Pancreas (Exocrine) Panel                                 |
| Hemoglobin                           | Pancreatic amylase                                               |
| Hematocrit                           | Lipase                                                           |
|                                      |                                                                  |
| Hepatic Chemistry/Coagulation | Lipid Panel (Fasting)                                     |
| Total bilirubin                      | Total cholesterol                                                |
| Direct bilirubin                     | LDL                                                              |
| Alkaline phosphatase                 | HDL                                                              |
| ALT                                  | Triglycerides                                                    |
| AST                                  |                                                                  |
| GGT                                  | HbA1c                                                     |
| PTT                                  |                                                                  |
| PT/INR                               | Fasting Plasma Glucose                                    |
| Albumin                              |                                                                  |
|                                      | Pregnancy test (serum or urine; females only)c |
| Endocrine                     |                                                                  |
| TSH                                  | Urine Chemistry                                           |
| FT4                                  | Creatinine                                                       |
| Calcitonin                           | Urine albumin/creatinine ratio (uACR)                            |
| C-peptide (fasting)                  |                                                                  |
| Estradiol a               |                                                                  |
| FSH b                     |                                                                  |

Abbreviations: FSH = follicle-stimulating hormone; HbA1c = hemoglobin A1c; HDL = high-density lipoprotein; LDL = low-density lipoprotein; RBC = red blood cells; VLDL = very low-density lipoprotein; WBC = white blood cells; ALT = alanine aminotransferase; AST = aspartate aminotransferase; CPK = creatinine phosphokinase; GGT = gamma-glutamyl transferase; PTT = Partial Thromboplastin Time; PT = Prothrombin Time; International Normalized Ratio (INR); TSH = Thyroid stimulating hormone; FT4 = free thyroxine.

a,bFSH test performed at Visit 1 (screening) for postmenopausal women of at least 45 years of age with an intact uterus, not on hormone therapy, and who have had spontaneous amenorrhea for more than six months and less than 12 months and estradiol levels consistent with a postmenopausal state (FSH  $\geq 40$  mIU/mL and estradiol  $< 30$  pg/mL).

cSerum pregnancy test (serum beta-hCG) will be performed during the screening visit. The result must be available before randomization and the first injection of the study drug for women of childbearing potential only. Additional pregnancy in urine tests will be performed during the study clinical visits.

dUrine albumin/creatinine ratio and estimated glomerular filtration rate (using the CKD-EPI formula) will be calculated by the central laboratory and included in laboratory result reports.

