### 9.3 Procedures at each visit

#### 9.3.1 Visit 1 – Screening.

After informed consent is obtained, the study staff will conduct vital signs and physical evaluation (including height and weight). The following procedures may be performed, data collected, and eligibility criteria checked and documented:

- Inclusion and exclusion criteria assessed.
- Demographics (year of birth, race/ethnicity, and gender).
- Diabetes and medical history (including severe hypoglycemia, DKA history, and microvascular complications).
- Substance use history (drinking, smoking, and drug habits).
- Prior and/or concomitant medications.
- Physical examination including weight, height, waist & hip circumference, waist-to-hip ratio, and vital signs (blood pressure, heart rate, and temperature).
- Electrocardiogram (ECG)
- Serum pregnancy test (serum beta-Hcg) for all females of child-bearing potential.
- Laboratory tests including Hb, hct, total serum bilirubin, direct bilirubin, indirect bilirubin, ALT, AST, ALP, PTT, PT, INR, GGT, serum albumin, pancreatic serum amylase, serum lipase, creatinine, eGFR (calculated by CKD-EPI), urine albumin/creatinine ratio (uCR), calcitonin, TSH, FT4, fasting plasma glucose (FPG) C-peptide (fasting), estradiol and FSH (if apply), TC, LDL, HDL, and triglycerides.
- HbA1c level measured using the DCA Vantage or similar point-of-care device/local lab.
- The study participant will receive a hypoglycemia diary to document clinically significant or severe (see **Annex 10** for hypoglycemia classification) hypoglycemia events, related symptoms, and precipitating activities such as meal omission, increased exercise frequency/intensity, or any other potential causes of hypoglycemia.
- AE/SAE assessment according to **Section. 10**.

Diabetes management information: We will record the participant's average total daily insulin use and total bolus insulin use (calculated over approximately two weeks), carbohydrate ratio, and correction factor (insulin sensitivity factor). Data from the participant's glucometer and CGM may be downloaded or recorded.

The participant will receive a study phone (if needed), an activity tracker (Fitbit sense 2), and the Dexcom G7 CGM system. The study apps (Fitbit app/SNAQ app) will be installed, and participants will receive training on their use. The study handbook also will be given to the participants.

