## Annex 7. Contraceptive Guidance and Collection of Pregnancy Information.

General definitions for contraceptive guidance can be found in **Table A2**.

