| Post-menopausal state               | 
The post-menopausal state is defined as:
 

(i) a woman at any age with at least six weeks post-surgical bilateral oophorectomy with or without hysterectomy, confirmed by operative note, or

(ii) a woman who is 40 to less than 55 years of age with an intact uterus, not on hormone therapy, who has cessation of menses for at least 12 months without an alternative medical cause, AND a follicle-stimulating hormone (FSH) >40 mIU/mL, or

(iii) a woman 55 years or older not on hormone therapy, who has had at least 12 months of spontaneous amenorrhea, or

(iv) a woman at least 55 years of age with a diagnosis of menopause before starting hormone replacement therapy.

 |

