| Women of non-childbearing potential                                                | Are not required to use contraception                                                                                                                                                                                                                                                                                                                                                                                                                                                                                                                                                                                                                                                                                                                                                                                                       |
| Women of childbearing potential (nonpregnant)                                      | 
MUST test negative for pregnancy before initiation of treatment as indicated by a negative serum pregnancy test at the screening visit, followed by repeated urine pregnancy tests during the study clinical visits.
 
AND
 
Use one NON-ORAL form of highly effective contraception listed in Table A3.
 
If a female participant is using ORAL contraceptives. They MUST switch to a non-oral method (e.g., vaginal ring or hormonal patch) OR use a barrier methoda for four weeks after starting tirzepatide for four weeks after each dose escalationb. Tirzepatide may reduce the effectiveness of oral hormonal contraceptives due to delayed gastric emptying, which is most pronounced after the first dose and diminishes over time.
 |

aOnly apply to female participants in the intervention group. Females in the control group with childbearing potential, who are using highly effective oral contraceptives, will continue their use without the need to switch for non-oral or additional barrier contraceptives.

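### Annex 6 orders FSH at screening in women for whom the Table A2 menopause definition cannot use it, and omits the women for whom Table A2 requires it

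*Protocol*

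**What the plan says.** **Who is tested.** Annex 6, footnote a,b sets the screening FSH test for women from age 45 who still have a uterus and take no hormone treatment, and already describes them as postmenopausal. Its amenorrhoea condition reads "spontaneous amenorrhea for more than six months and less than 12 months and estradiol levels consistent with a postmenopausal state". The hormone limits it gives are FSH of 40 mIU/mL or more and estradiol below 30 pg/mL.

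**Who counts as post-menopausal.** Annex 7 points the reader to Table A2 with the words "General definitions for contraceptive guidance can be found in". That table gives four routes to the post-menopausal state:

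- (i) Bilateral oophorectomy, at any age.
- (ii) Age 40 to under 55, uterus in place and no hormone treatment. The further condition is worded "who has cessation of menses for at least 12 months without an alternative medical cause, AND a follicle-stimulating hormone (FSH", and the level has to exceed 40 mIU/mL.
- (iii) "a woman 55 years or older not on hormone therapy, who has had at least 12 months of spontaneous amenorrhea".
- (iv) Age 55 or over, with menopause diagnosed before hormone replacement began.

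**What follows from the status.** Table A4 lifts the contraception requirement for "Women of non-childbearing potential". Women of childbearing potential must use contraception, have a negative serum pregnancy test at screening and repeat urine tests at clinic visits.

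**Other mentions of FSH.** Section 9.3.1 lists "estradiol and FSH (if apply") without saying to whom it applies. Table 1, footnote g lists FSH and refers back to Annexes 6 and 6.1. Annex 6.1 is a plain list of tests by visit.

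**The concern.** FSH is on the screening panel to help decide whether a woman can still become pregnant. That works only if the women tested are those whose classification depends on the result. Here the footnote stops below 12 months of amenorrhoea, and the only Table A2 route that uses FSH starts at 12 months.

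Two errors can follow:

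- **Safe direction.** A 50-year-old with 14 months of amenorrhoea is not in the footnote's group. Without an FSH result she cannot meet route (ii). She stays classed as of childbearing potential, with contraception and pregnancy tests she may not need.
- **Unsafe direction.** A 47-year-old with 8 months of amenorrhoea, FSH 45 mIU/mL and estradiol 20 pg/mL fits the footnote's description and carries its postmenopausal label. Under Table A2 she is of childbearing potential. A site that acted on the label could drop her contraception and pregnancy tests while she takes a drug for which Section 3.7 notes possible fetal risk.

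**Working it through.** The plan gives no figure to reproduce here. The check compares the two rules and then sizes the groups.

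**1. Which Table A2 routes can use the footnote's result?** Take a woman in the footnote's group: 45 or over, uterus in place, no hormone treatment, natural amenorrhoea between 6 and 12 months.

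| Route | Uses FSH? | Open to her? |
|---|---|---|
| (i) oophorectomy | No | No, surgical |
| (ii) age 40 to under 55, at least 12 months | Yes | No, under 12 months |
| (iii) age 55 or over, at least 12 months | No | No, under 12 months |
| (iv) menopause before hormone replacement | No | No, she takes none |

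One route of four uses FSH, and none can use a result from this group.

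**2. Grid check.** Inputs: the trial's age range of 18 to 65 (Section 7.1.1), 0 to 36 whole months of natural amenorrhoea, uterus in place, no hormone treatment.

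- The footnote orders FSH at ages 45–65 and months 7–11: 21 × 5 = 105 cells.
- FSH changes Table A2 status at ages 40–54 and months 12–36: 15 × 25 = 375 cells.
- Cells in both sets: 0.

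The zero does not depend on the grid, because under 12 months and at least 12 months exclude each other at any age.

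**3. Other differences between the two texts.**

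| Item | Annex 6 footnote | Table A2 (ii) |
|---|---|---|
| Age | 45 or over, no upper limit | 40 to under 55 |
| Amenorrhoea | More than 6, less than 12 months | At least 12 months |
| FSH | 40 mIU/mL or more | Above 40 mIU/mL |
| Estradiol | Below 30 pg/mL | Not used |

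The footnote also describes the women to be tested partly by the hormone results themselves, so it does not work as an ordering rule.

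**4. How many women.** The protocol gives no sex or age mix, so every proportion below is an assumption. The totals of 42 participants and 21 per arm come from Section 11.2.

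*Safe direction, both arms.* Count = 42 × share of women × share of them aged 40–54 × share of those with at least 12 months of natural amenorrhoea.

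- Low: 42 × 0.40 × 0.25 × 0.10 = 0.42
- High: 42 × 0.60 × 0.40 × 0.30 = 3.02

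*Unsafe direction, tirzepatide arm.* Count = 21 × share of women × share of them aged 45 or over × share of those in the 6 to 12 month window.

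- Low: 21 × 0.40 × 0.20 × 0.03 = 0.05
- High: 21 × 0.60 × 0.40 × 0.10 = 0.50

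**The case against.** The case on the other side has four parts.

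- **The footnote does not forbid testing anyone else.** Table 1, footnote g and Annex 6.1 list FSH at Visit 1 without restriction, and Table A2 (ii) itself gives a site reason to test a 50-year-old with 14 months of amenorrhoea. This stands in part: a site could test the right women. No text tells it to, however. Footnote g points back to the annex that holds the faulty rule, and Section 9.3.1 leaves applicability open.
- **The unsafe path needs staff to set aside clear text.** The footnote concerns laboratory tests and says nothing about contraception. The eligibility criteria and Section 8.6 send the reader to Annex 7. This stands, and it is why the unsafe direction is stated as conditional.
- **The counts are soft and lean high.** The unsafe count takes misreading as certain and ignores the footnote's FSH and estradiol limits. The safe count does not remove women who are surgically sterilised, in exclusively same-sex relationships or on hormone treatment, and it supposes that no site orders FSH on its own initiative. All of this stands. The figures show only that few women are involved.
- **It is a mismatch between annexes with no effect on the analysis.** True. But it is an instruction that gives the wrong result when followed as written, in a rule meant to protect against fetal exposure.

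**Conclusion.** The inconsistency is real and does not depend on any assumption: the women the footnote tests and the women in whom FSH decides Table A2 status have no overlap. Treating Table A2 as the controlling definition is an inference from the opening of Annex 7, but a firm one, because the contraception requirements in Table A4 rest on it.

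The consequence is small. Table A2 still classifies every woman, and the default error is unneeded precaution for roughly 0 to 3 participants. The unsafe error concerns at most about half a woman in expectation, even if misreading were certain. Nothing in the efficacy endpoints, sample size or analysis changes. The text should be corrected because it is wrong as written and cheap to put right.

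**What to change.** Keep Table A2 as the single definition and bring Annex 6, footnote a,b into line with route (ii):

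- Order FSH at Visit 1 for women from age 40 up to their 55th birthday who have a uterus, take no hormone treatment and have had no menses for 12 months or longer without another medical explanation.
- State that post-menopausal status then requires FSH above 40 mIU/mL, with a reference to Table A2.
- Delete the 6 to 12 month description, its postmenopausal label and the estradiol condition.
- Add that women with less than 12 months of amenorrhoea are handled as of childbearing potential unless another Table A2 route applies.

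Estradiol would then have no stated purpose at screening. Unless it serves another one, remove it from Table 1 footnote g, Section 9.3.1, Annex 6 and Annex 6.1.

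The cost is a footnote rewrite and these consequential edits. FSH is already listed for Visit 1, so no new assay or visit is needed.

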## Annex 6.1 Clinical Laboratory Test

| Clinical Laboratory Test per visit    |                                       |
|---------------------------------------|---------------------------------------|
| Visit 1 – Screening                   | Visit 3 – Follow-up                   |
| Hemoglobin                            | Total bilirubin                       |
| Hematocrit                            | Direct bilirubin                      |
| Total bilirubin                       | Indirect bilirubin                    |
| Direct bilirubin                      | ALT                                   |
| Alkaline phosphatase                  | AST                                   |
| ALT                                   | Pancreatic amylase                    |
| AST                                   | Serum Lipase                          |
| GGT                                   | Creatinine                            |
| PTT                                   |                                       |
| PT/INR                                | Visit 4 – Last Visit                  |
| Serum Albumin                         | ALT                                   |
| TSH                                   | AST                                   |
| FT4                                   | Direct bilirubin                      |
| Calcitonin                            | Total bilirubin                       |
| C-peptide (fasting)                   | Indirect bilirubin                    |
| Estradiol                             | Calcitonin                            |
| FSH                                   | Serum Pancreatic amylase              |
| Serum Pancreatic amylase              | Serum Lipase                          |
| Serum Lipase                          | Total cholesterol                     |
| Total cholesterol                     | LDL                                   |
| LDL                                   | HDL                                   |
| HDL                                   | Triglycerides                         |
| Triglycerides                         | Urine albumin/creatinine ratio (uACR) |
| HbA1c                                 | HbA1c                                 |
| Serum pregnancy test (serum beta-hCG) |                                       |
| Urine albumin/creatinine ratio (uACR) |                                       |

## Annex 7. Contraceptive Guidance and Collection of Pregnancy Information.

General definitions for contraceptive guidance can be found in **Table A2**.

**Table A2. General Definitions**

| Word/Phrase                         | Definition                                                                                                                                                                                                                                                                                                                                                                                                                                                                                                                                                                                                                                                                                                                                                                                  |
|-------------------------------------|---------------------------------------------------------------------------------------------------------------------------------------------------------------------------------------------------------------------------------------------------------------------------------------------------------------------------------------------------------------------------------------------------------------------------------------------------------------------------------------------------------------------------------------------------------------------------------------------------------------------------------------------------------------------------------------------------------------------------------------------------------------------------------------------|
| Women not of childbearing potential | 
Females are considered women not of childbearing potential:
 

(i) after menopause

(ii) before the menarche

(iii) if they have a congenital anomaly such as Mullerian agenesis with primary amenorrhea, or

(iv) who are infertile due to surgical sterilization.

 
Examples of surgical sterilization include:
 

(i) hysterectomy

(ii) bilateral oophorectomy, and

(iii) tubal ligation.

                                                                                                                                                                                                                                              |
| Post-menopausal state               | 
The post-menopausal state is defined as:
 

(i) a woman at any age with at least six weeks post-surgical bilateral oophorectomy with or without hysterectomy, confirmed by operative note, or

(ii) a woman who is 40 to less than 55 years of age with an intact uterus, not on hormone therapy, who has cessation of menses for at least 12 months without an alternative medical cause, AND a follicle-stimulating hormone (FSH) >40 mIU/mL, or

(iii) a woman 55 years or older not on hormone therapy, who has had at least 12 months of spontaneous amenorrhea, or

(iv) a woman at least 55 years of age with a diagnosis of menopause before starting hormone replacement therapy.

 |

